## Abstract

**Background:** In Germany, the nutritional situation of adults and children living in households at risk of poverty has been insufficiently studied so far. **Aim:** The aim of the mixed-methods study MEGA_kids is to gain a deeper understanding of the nutritional situation including socioeconomic, behavioral, and attitudinal factors and health characteristics among persons living in families at risk of poverty. **Method:** MEGA_kids is a mixed-methods cross-sectional study consisting of four modules combining quantitative and qualitative methods. The first module (A) applies self-administered questionnaires to assess the individual's diet, household food insecurity, and several other factors among adults and children of 500 households. Cash receipts are used to assess household's food expenses. For the second module (B), a semistructured interview guide is used to identify factors influencing food security and nutritional quality from the perspective of a subsample of module A (n = 20). The third module (C) applies the participatory World Café technique to explore experiences and generate ideas for tailored support measures for a healthy diet from the perspective of 40 parents participating in module A. Finally, the fourth module (D) investigates the knowledge and usage of existing nutrition-related preventive measures among 200 parents at risk of poverty by using an online questionnaire. **Conclusion:** By providing a comprehensive picture of nutritional aspects of families living at risk of poverty, MEGA_kids will guide officials to target and prioritize public health nutrition measures, inform policy makers to implement and improve healthy policies and, finally, identify research gaps to be prioritized.

## Introduction

In 2021, nearly 16% of the population were at risk of poverty in Germany, that is, roughly 13 million people have an equivalized disposable income below the at risk of poverty threshold, which is set at 60% of the national median equivalized disposable income after social transfers. People at a particular high risk of poverty include children, single parents, households with three or more children and people aged at least 65 years (Federal Statistical Office, 2022b).

The persistent link between poverty and disadvantaged health outcomes among adults and children has been well documented by national (Lampert and Kuntz, 2019; Pförtner and Schumann, 2016) and international studies (Gupta et al., 2007; Raphael, 2011). Nutrition plays a critical role in this association. For instance, the consumption of fruit and vegetables is inversely related to the risk of hypertension, coronary heart disease, and stroke (Boeing et al., 2012). Children and adults at risk of poverty tend to consume less fruit and vegetables than their wealthier counterparts (Grimm et al., 2012; Lampert and Kuntz, 2019). Thus, differences in the nutritional status may partly explain differences in health outcomes.

From a life course perspective, the nutrition during childhood is of particular importance. Nutritional preferences and eating habits established in childhood tend to be maintained in adulthood (Chong, 2022; Mikkilä et al., 2004). Moreover, nutrition in childhood has lasting effects on health in adulthood (Caballero, 2001; Kaikkonen et al., 2013). Children growing up in families at risk of poverty may therefore have a higher risk of negative health outcomes in adulthood, which in turn increases the risk of poverty as an adult (Mader et al., 2020). Despite these findings, there are only few studies illuminating the nutrition of children and adults living in households at risk of poverty in Germany.

While national surveys such as the German National Nutrition Survey II (NVS II) (Heuer et al., 2015), the German health interview and examination survey for adults (DEGS) (Mensink et al., 2017) and the German Health Interview and Examination Survey for Children and Adolescents (KiGGS) (Finger et al., 2015; Mensink et al., 2020) have revealed differences in the nutrition status between income or socioeconomical groups, they are not designed to provide a detailed picture of the nutrition status of families at risk of poverty. For instance, the DEGS questionnaires were available in Russian, Turkish, Serbo-Croatian, and English only (Gößwald et al., 2012), whereas migrants being born in Arabic countries such as Syria were among those with the highest at-risk of poverty rate (Federal Statistical Office, 2022a). Results of KiGGS may be influenced by a selection bias, as parents of respondents had, on average, a higher educational level compared to parents of nonrespondents (Hoffmann et al., 2018). Due to the written questionnaires, parents with reduced literacy may have lower chances to participate compared to parents with sufficient literacy skills (Lampert and Kuntz, 2019). In addition, none of these surveys covered poverty-related topics such as food insecurity.

Other studies have presented qualitative information about the relationship between deprived material circumstances and aspects of the nutrition such as meal preparation and food shopping (Lehmkühler, 2002; Pfeiffer et al., 2015; Yildiz, 2014). Few quantitative studies on people at risk of poverty have focused on specific population groups such as food bank users or homeless people in selected cities (Depa et al., 2015, 2018; Langnäse and Müller, 2001). However, a detailed picture of the nutritional situation of children and adults living in households at risk of poverty is still missing in Germany.

To gain a deeper understanding of the nutritional situation of persons living in families at risk of poverty including socioeconomic, behavioral, and attitudinal factors, and health characteristics, and to explore experiences, perspectives, and ideas regarding a healthy diet, the “Multidisciplinary study of the health and nutritional status of persons living in households at risk of poverty with children in Germany” (MEGA_kids) is conducted. In this article, the rationales for this study as well as its methods are described.

## Methods

### Study design

MEGA_kids is a mixed-methods cross-sectional study combining four study modules (Table 1):
The first module (BERNA, “Nutritional survey among individuals living in households at risk of poverty with children”) contains a cross-sectional survey among children, youths, and adults living in households at risk of poverty. By this module, food intake, food insecurity as well as other nutritional and health aspects such as cooking skills, nutritional knowledge, and subjective health is assessed by standardized questionnaires. In addition, participants are asked to collect their cash receipts of food shopping over a period of 2 weeks.For the second module (IDEE, “Identification of factors influencing food security and nutritional quality from the perspective of adults living in households at risk of poverty with children”) a subsample of adults from BERNA is drawn with whom semistructured interviews are conducted about the food provision and preparation in everyday life as well as the social and health dimension of nutrition in their household.For the third module (BEA, “Needs of households at risk of poverty with children and approaches to develop behavioral and environmental support measures for a healthy diet“), another subsample of adults from BERNA is drawn and focus groups using the World Café technique are conducted to identify opinions and experiences, and generate ideas for tailored support measures for a healthy diet from the perspective of the adult target group.Finally, the fourth module (KENNER, “Knowledge and usage of nutrition-related preventive measures among adults of households with children at risk of poverty”) is a cross-sectional survey among parents living in households at risk of poverty about their knowledge regarding and usage of existing nutrition-related measures.

**Table 1. table1-02601060241242159:** Modules of MEGA_kids.

**Name**	**Sampling**	**Design**	**Duration**	**Sample size**
BERNA (“Nutritional survey among individuals living in households at risk of poverty with children”)	Multistage, partly randomized	Standardized survey (self-administered questionnaires + collecting cash receipts over 2 weeks)	ca. 20–40 min	1000 individuals (500 adults and 500 children) of 500 households
KENNER (“Knowledge and usage of nutrition-related preventive measures among adults of households at risk of poverty with children”)	Multistage, partly randomized	Standardized survey (online-questionnaire/standardized interview)	ca. 20 min	200 adults of 200 households
IDEE (“Identification of factors influencing food security and nutritional quality from the perspective of adults living in households at risk of poverty with children”)	Convenience, subsample von BERNA	Semistructured individual interview	ca. 60–120 min	20 adults of 20 households
BEA (“Needs of households at risk of poverty with children and approaches to develop behavioral and environmental support measures for a healthy diet”)	Convenience, subsample of BERNA	Participatory World Café discussions in small groups	ca. 120 min	2 × 20 adults of 2 × 20 households

### Study population

#### Quantitative module BERNA

The study population comprises children aged between 1 and 17 years as well as adults over the age of 18 years living in households at risk of poverty with children in rural and nonrural districts in Germany.

To illustrate the wider range of income-related risk of poverty, eligible households must meet at least one of the following criteria:
- household has an equivalized disposable income at or below the at risk of poverty thresholds (60% of the national median equivalized disposable income) and/or- household head receives social transfers including, for instance, unemployment pay II, and/or- household receives food assistance from a food bank.

Households of separated parents with shared custody are able to participate if at least one child lives for at least 15 of 28 days in this household. In households with more than one adult, the adult who is responsible for the majority of food shopping is allowed to participate.

The adult has to be sufficiently able to speak or write German, English, or Arabic. Adolescents must be able to speak or write German.

Information for children between 1 and 11 years are obtained by adults (parents), whereas adolescents between 12 and 17 years can participate themselves.

Households headed by a pregnant woman are excluded from participation. In addition, persons living in “collective living quarters” or other shared accommodations are excluded.

The sample of BERNA is expected to include 500 adults and 500 children aged between 1 and 17 years.

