In the third step, individuals visiting the facilities are recruited by active and/or passive recruitment strategies. In facilities with a high traffic of families being at risk of poverty such as food banks, job centers and most social supermarkets, a combination of both recruitment strategies is applied. Each facility that agreed to participate is visited twice by trained study staff. Before the first visit, facilities’ officials are asked to hang out posters and leaflets describing the study and advertising the upcoming visit of the study team. During the visit, all adults visiting the facility are informed about the aim, the study procedures, and data protection measures, verbally and by a printed study information sheet. People willing to participate are screened for inclusion into the study using a checklist. In households with more than one child, the oldest child between 1 and 17 years is able to participate. Parents willing to participate are asked to complete the informed consent form and are given the study materials including a short instruction, the study information for parents and, if applicable, for youths, all questionnaires, and a small bag for collecting cash receipts. Parents are asked whether they are available 2 weeks later to return the answered questionnaires and the collected cash receipts. If parents are not available at this date, they are given a stamped return envelope. Two weeks later, the facilities are visited again. Answered questionnaires are controlled for completeness and plausibility. People, who have not visited the facility during the first visit, are invited to participate during the second visit. If eligible and willing to participate, study materials are handed out and the participants are given a stamped return envelope.

In facilities with lower traffic of families such as counseling centers or those with unspecific traffic of families, such as kindergartens, leaflets are given to staff and they are asked to hand out the leaflet to families. The leaflets briefly describe the study procedure and provide contact details. Families willing to participate are screened by phone or by e-mail and the study materials are sent by post.

Participants receive a remuneration of 7,50 Euro for completing the parents’ version of the questionnaires, additional 7,50 Euro for completing the child/youth version of the questionnaires and additional 5 Euro for collecting cash receipts.

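### BERNA surveys the oldest child without requiring that this child meets the shared-custody residence rule, and states no fallback when that child is an adolescent without German

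*Protocol article*

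**What the plan says.** All references are to the protocol article, Methods.

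- **Residence (Study population, BERNA).** Households of separated parents sharing custody may take part "if at least one child lives for at least 15 of 28 days in this household". This condition is set on the household. The target population is described only as people "living in households at risk of poverty with children in rural and nonrural districts in Germany", with no number of days for the individual child.
- **Which child (Procedure, BERNA).** "In households with more than one child, the oldest child between 1 and 17 years is able to participate".
- **Language (Study population, BERNA).** "The adult has to be sufficiently able to speak or write German, English, or Arabic". For the young participants: "Adolescents must be able to speak or write German".
- **Who answers (Study population, BERNA).** "Information for children between 1 and 11 years are obtained by adults (parents), whereas adolescents between 12 and 17 years can participate themselves".
- **Planned sample (Study design, Table 1).** "1000 individuals (500 adults and 500 children) of 500 households".
- **Measurement and analysis.** The child and youth food frequency questionnaires cover the past 4 weeks. Food insecurity is a household measure over the past 30 days. Income is recorded per household, and receipts cover 2 weeks of the family's food shopping. The Analyzes section plans mixed models relating diet to food insecurity and other factors.

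**The concern.** The residence threshold appears to be there so that the child belongs mainly to the household being described. Its 28-day window has the same length as the recall period of the diet questionnaire. It can do that job only if it applies to the child whose diet is reported. As written, one child can qualify the household and a different child can be surveyed.

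For such a child, the diet record describes meals eaten largely in another home, while the food insecurity, income and receipts describe this one. That error goes straight into the planned diet–food-insecurity models. It would probably weaken the estimated association, and a random effect for clustering does not repair it.

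The language rule raises a related but weaker problem. The oldest-child rule steers selection towards adolescents, the only participants who must manage in German. When the selected adolescent cannot, the article does not say whether to take a younger, parent-reported sibling, enrol the adult alone, or exclude the household. The Discussion mentions language as a limitation for the qualitative modules only.

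**Working it through.** **1. The plan's own count.** From Table 1: 500 households, one adult and one child each. 500 × (1 + 1) = 1000, which matches the stated total. It matches only if every household yields exactly one child record.

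**2. Residence rule against oldest-child rule.** Take a shared-custody household with two children. The threshold is 15/28 = 53.6% of days; a child below it is present at most 14/28 = 50%.

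| Oldest child, days | Younger child, days | Household qualifies | Child surveyed | Surveyed child meets the threshold |
|---|---|---|---|---|
| 15 or more | 15 or more | yes | oldest | yes |
| 15 or more | 14 or fewer | yes | oldest | yes |
| 14 or fewer | 15 or more | yes | oldest | **no** |
| 14 or fewer | 14 or fewer | no | none | – |

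One pattern of the four goes wrong, and it needs siblings on different schedules.

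The number of such records is 500 × a × b × c, where
- a = share of households that are shared-custody with two or more children,
- b = share of those whose children follow different schedules,
- c = share of those in which the oldest falls below the threshold and a younger child reaches it.

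The article gives none of the three. For scale only: each 1% of households affected is 500 × 0.01 = 5 child records.

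**3. Language rule against oldest-child rule.** Let q be the share of households whose oldest child is aged 12–17, and s the share of those adolescents who can neither speak nor write German. Both are assumptions. If such a household is enrolled with the adult alone:

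- child records from 500 households = 500 × (1 − q × s)
- households needed for 500 child records = 500 / (1 − q × s), rounded up

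| q | s | q × s | Child records | Households needed |
|---|---|---|---|---|
| 0.3 | 0.02 | 0.006 | 497 | 504 |
| 0.4 | 0.10 | 0.040 | 480 | 521 |
| 0.5 | 0.20 | 0.100 | 450 | 556 |

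These are illustrations, not estimates. They count every such household as lost, including those with no eligible younger sibling, where a fallback could not help. If the household is instead treated as ineligible and replaced, 500 child records remain attainable, but those families leave the survey altogether. The article does not say which applies.

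**The case against.** The strongest reply is that the text can be read sensibly in sequence: people are screened with a checklist first, and the oldest child is then chosen among those who live in the household and qualify. The checklist is not shown, and an article condenses a fuller protocol. This carries weight for the missing language fallback, which on its own would be an operational detail. It carries less for residence. There the article states two explicit rules, one satisfied by any child and one naming the oldest child aged 1–17, and followed literally they can select a child who does not meet the threshold.

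Other parts of the reply stand and limit the point:

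- Siblings who move together between homes cause no error.
- The adapted questionnaire asks with whom the child mainly lives (Data collection, BERNA), so many affected children can be identified. It is not a day count, however, and may miss an even split.
- The 15-day threshold itself still admits a child who spends up to 13 of 28 days elsewhere, so applying it per child limits the mismatch without removing it.
- BERNA is first a descriptive survey, with the association models added.

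A reader might infer three stronger claims that the document does not support:

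- **That the language rule misses the surveyed child.** It does apply to the surveyed adolescent; only the fallback is unstated.
- **That children of recent immigrants are broadly lost.** Children aged 1–11 are reported by a parent, who may use German, English or Arabic. Adolescents need only speak or write German, and participants needing help are interviewed.
- **That 25–50 records are affected.** That would follow from assuming 5–10% of 500 households and counting every multi-child shared-custody home as wrong, which is the wrong group.

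**Conclusion.** The point holds in a limited form. The residence rule and the oldest-child rule do not fit together, and as written they can attach a child's diet to a household where he or she does not mainly live. This requires shared custody, at least two children, different schedules, and an oldest child below the threshold. Separately, no fallback is stated when the oldest child is an adolescent without German, so one child per household is not guaranteed.

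The size cannot be derived from the article and is probably small. The 450–497 child records in the language illustration rest wholly on assumed shares. Attenuation of the diet–food-insecurity association is likely in direction but not quantifiable here.

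Nor does the document support saying that the sample of 500 children fails: it is stated as an expectation, with no power calculation given, so a modest shortfall breaches no stated precision or power target. The point is worth correcting because the remedy is nearly free and the BERNA data are to be made public, so later users need to know which child was surveyed.

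**What to change.** **If recruitment is still open:** define the index child as the oldest child aged 1–17 who individually lives in this household at least 15 of 28 days and, if aged 12–17, can speak or write German. If the oldest child does not qualify, take the next oldest who does. This costs one line on the screening checklist.

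**If recruitment is complete** (data collection was due to end in June 2023):

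- State which child was taken when the oldest did not qualify.
- Use the item on with whom the child mainly lives to flag surveyed children living mainly elsewhere. Exclude them from the household–child association models, at least as a sensitivity analysis.
- Report the number of households without a child record.
- Describe 500 children as the expected maximum.
- Carry the flag into the public dataset.

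The cost is one derived variable, one additional model run and a few child records lost from the association models. Diet descriptions of the children themselves need not change.

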#### Qualitative modules BEA and IDEE and quantitative module KENNER

The qualitative modules BEA and IDEE and the quantitative module KENNER apply the same inclusion and exclusion criteria, but only adults who are sufficiently able to speak German are eligible to participate.

In BEA, one World Café is conducted with adults living in a rural district and another with adults living in a nonrural district. The sample of IDEE interview partners should include eight participants living in nonrural districts as well as six each in rural districts with a good and a worse socioeconomic condition. The sample of KENNER is expected to include 200 adult participants.

### Procedure

The data collection period of the MEGA_kids projects started in April 2022 and will be finished in June 2023.

#### Quantitative module BERNA

Participants of the BERNA survey are enrolled in three steps. In the first step, eleven districts throughout Germany are randomly drawn, stratified by the typology for rural areas of the Thünen Institute (Küpper, 2016). By combining the two dimensions rurality and socioeconomic condition, the Thünen Institute assigned each district to one of the following five types: nonrural, very rural and good socioeconomic condition, rural and good socioeconomic condition, very rural and worse socioeconomic condition and rural and worse socioeconomic condition (Küpper, 2016). For the purpose of this study, very rural and rural districts are combined resulting in three strata. Overall, five nonrural, three very rural/rural districts with good socioeconomic condition and three very rural/rural districts with worse socioeconomic condition are randomly drawn.

In the second step, facilities serving low-income population groups including, for instance, food banks (“Tafel”), job centers, family centers, social supermarkets, facilities providing employment measures for long-term unemployed individuals, and others are selected in each district. In addition, in each nonrural and very rural/rural district with worse socioeconomic condition, a random sample of five childcare facilities is drawn. Managers of all selected facilities receive written information about the study including its aim and procedure and are asked to allow the recruitment of families visiting the facility. A sampled rural district with good socioeconomic condition is included if at least one food bank and one other social facility are willing to participate and rural districts with worse socioeconomic condition and a nonrural area is included if at least one food bank, one childcare facility, and two social facilities agree to participate in the study. In doing so, a minimum of 38 facilities are included in the study.

In the third step, individuals visiting the facilities are recruited by active and/or passive recruitment strategies. In facilities with a high traffic of families being at risk of poverty such as food banks, job centers and most social supermarkets, a combination of both recruitment strategies is applied. Each facility that agreed to participate is visited twice by trained study staff. Before the first visit, facilities’ officials are asked to hang out posters and leaflets describing the study and advertising the upcoming visit of the study team. During the visit, all adults visiting the facility are informed about the aim, the study procedures, and data protection measures, verbally and by a printed study information sheet. People willing to participate are screened for inclusion into the study using a checklist. In households with more than one child, the oldest child between 1 and 17 years is able to participate. Parents willing to participate are asked to complete the informed consent form and are given the study materials including a short instruction, the study information for parents and, if applicable, for youths, all questionnaires, and a small bag for collecting cash receipts. Parents are asked whether they are available 2 weeks later to return the answered questionnaires and the collected cash receipts. If parents are not available at this date, they are given a stamped return envelope. Two weeks later, the facilities are visited again. Answered questionnaires are controlled for completeness and plausibility. People, who have not visited the facility during the first visit, are invited to participate during the second visit. If eligible and willing to participate, study materials are handed out and the participants are given a stamped return envelope.

In facilities with lower traffic of families such as counseling centers or those with unspecific traffic of families, such as kindergartens, leaflets are given to staff and they are asked to hand out the leaflet to families. The leaflets briefly describe the study procedure and provide contact details. Families willing to participate are screened by phone or by e-mail and the study materials are sent by post.

Participants receive a remuneration of 7,50 Euro for completing the parents’ version of the questionnaires, additional 7,50 Euro for completing the child/youth version of the questionnaires and additional 5 Euro for collecting cash receipts.

